#### Sample size determination and accrual plan

3.6.2

Although this is a descriptive cohort study, a formal sample size calculation was performed for a secondary objective of particular significance: the development of a multivariable prediction model for in-hospital mortality. In accordance with the widely accepted criterion of a minimum of 10 events per predictor variable for logistic regression, and anticipating up to 10 potential predictors, a minimum of 100 mortality events is required. Utilizing a conservative estimated mortality rate of 12.6% as derived from previous studies, it is estimated that a total cohort of at least 794 patients would be required to achieve the desired statistical power. To account for potential incomplete data and to ensure adequate power for other secondary analyses, the target sample size is set at 1,000 patients.

The enrollment target is supported by historical annual NICU admissions across the nine high-volume tertiary centers and by pilot accrual data from the coordinating center. Together, these data indicate feasibility within the planned four-year recruitment window (2025–2028). The enrollment-monitoring framework that will be implemented includes quarterly accrual reviews and formal feasibility assessments at 12 and 24 months. In the event that accrual falls below pre-defined thresholds, pre-specified contingency measures are to be enacted. The following measures are to be implemented: activation of up to 1–3 pre-identified tertiary centers in Shenzhen, Guangdong Province; temporary augmentation of research-coordinator full-time equivalents at underperforming sites to improve case ascertainment and data capture; and structured extension of the recruitment period, subject to steering-committee and ethics-committee approval. These measures are intended to ensure the viability of the study while maintaining methodological rigor.

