### Statistical analysis plan

6.1

Continuous variables will be summarized as mean ± standard deviation (SD) or median with interquartile range (IQR), depending on distribution. Categorical variables will be presented as frequencies and percentages. Group comparisons will be conducted using the student's *t*-test or Mann–Whitney *U* test for continuous variables, and the *χ*² test or Fisher's exact test for categorical variables.

Univariate logistic regression will be used to examine associations between NARDS and study outcomes. Multivariable logistic regression will then be performed to identify independent predictors. Missing data will be addressed primarily using multiple imputation by chained equations (MICE), assuming data are missing at random. Variables with excessive missingness will be excluded according to predefined thresholds, and the imputation model will be structured accordingly. Sensitivity analyses will include complete-case analysis, k-nearest neighbors (k-NN) imputation, and inverse probability weighting to evaluate the robustness of findings to loss to follow-up. A two-sided *p* < 0.05 will be considered statistically significant. All analyses and visualizations will be conducted using R software (version 4.3.3).

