### Machine learning and predictive modeling

6.2

Beyond conventional regression, predictive modeling will employ a suite of algorithms, including penalized logistic regression (Elastic Net), decision trees, random forests, gradient boosting machines, support vector machines, and artificial neural networks. Two primary prediction tasks will be addressed: Early identification of neonates at risk of severe NARDS (OI > 16 within 72 h of diagnosis); Long-term prognosis (mortality, NDI, SRM, or growth restriction at the 24- and 36-month corrected age). Candidate predictors will be selected based on clinical relevance and temporal availability (within 24 h for early warning models; within 7 days for prognostic models). Feature selection and regularization will primarily use Elastic Net. To identify novel NARDS endotypes, Integrative Multi-Omics Factor Analysis (MOFA) or similar unsupervised data integration approaches [e.g., sparse Partial Least Squares Discriminant Analysis (sPLS-DA)] will be employed to identify latent factors and co-varying molecular pathways across omics layers. These integrated molecular signatures will subsequently serve as input features for downstream machine learning models (e.g., Random Forest) to construct highly discriminative and biologically informed predictive classifiers.

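### The 10-events-per-predictor calculation supports only a 10-candidate in-hospital mortality model on the full cohort, a limit that the modelling sections do not carry

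*Protocol article*

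**What the plan says.** Section 3.6.2 ties the sample size to one secondary objective, "the development of a multivariable prediction model for in-hospital mortality". The rule is "a minimum of 10 events per predictor variable for logistic regression", applied as "anticipating up to 10 potential predictors, a minimum of 100 mortality events is required". The event rate follows: "Utilizing a conservative estimated mortality rate of 12.6% as derived from previous studies". The result is that "a total cohort of at least 794 patients would be required". The target is then raised to 1,000 to allow for incomplete data and, the text adds, to give enough power for further secondary analyses. No calculation is shown for those.

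The analysis sections describe the modelling as follows:

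- **6.1:** univariate logistic regression first. Then: "Multivariable logistic regression will then be performed to identify independent predictors". No list or maximum number is given.
- **6.2:** two primary prediction tasks, severe NARDS within 72 h and long-term prognosis at 24 and 36 months. "Candidate predictors will be selected based on clinical relevance and temporal availability", and "Feature selection and regularization will primarily use Elastic Net". Tree-based, support-vector and neural-network learners are also planned, with multi-omics signatures as inputs.
- **6.3 and 6.4:** a random split into 70% for development and 30% for validation. Section 6.3 also plans cross-validation and bootstrap resampling.

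**The concern.** An events-per-predictor rule protects against overfitting only if it counts every parameter that had a chance to enter the model, not just those that remain after selection. The word potential in 3.6.2 suggests that the 10 is meant as a candidate count. No analysis section holds the mortality model to it, names the 10, or says whether that model is fitted on the full cohort or on the 70% set.

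If the pool is larger than 10, or the development set smaller than 1,000, the model falls below the plan's own minimum while the sample size section suggests that it is met. Selection would then be less stable. Effects reported for selected predictors would tend to be exaggerated, and their p-values too small.

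A reader may also take 1,000 as justified for the two prediction tasks in 6.2 and for the omics models. The calculation does not address them.

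**Working it through.** **Inputs from the protocol article.** Events per predictor: 10 (3.6.2). Potential predictors: 10 (3.6.2). Mortality: 12.6% (3.6.2). Target: 1,000 (3.6.2). Development fraction: 70% (6.3, 6.4).

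**Step 1: the plan's own figure.** Events needed = 10 × 10 = 100. N = 100 / 0.126 = 793.65, rounded up to 794. This reproduces exactly.

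**Step 2: the sized model at the target.** Expected deaths = 1,000 × 0.126 = 126. Per parameter with 10 candidates: 126 / 10 = 12.6. The rule is met in the full cohort.

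**Step 3: the same model in the 70% set.** Expected deaths = 0.7 × 126 = 88.2. Per parameter: 88.2 / 10 = 8.8. The rule is narrowly missed with exactly 10 candidates. Meeting it there would need 100 / (0.126 × 0.7) = 1,133.8, so 1,134 infants.

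**Step 4: more than 10 candidates.** The protocol gives no number, so the counts k below are assumptions. Deaths per parameter are 126 / k in the full cohort and 88.2 / k in the 70% set. The N that meets the rule in the full cohort is 10k / 0.126.

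| Candidates k | Full cohort | 70% set | N needed, full cohort |
|---|---|---|---|
| 10 | 12.6 | 8.8 | 794 |
| 20 | 6.3 | 4.4 | 1,588 |
| 30 | 4.2 | 2.9 | 2,381 |
| 37 | 3.4 | 2.4 | 2,937 |

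The last row is an upper illustration from Table 1: 7 perinatal + 11 neonatal + 3 severity scores + 5 comorbidities + 12 laboratory items = 38. Umbilical artery blood gas is listed twice, which leaves 37 distinct items. Each panel, such as the blood count, counts as one.

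**Step 5: sensitivity to mortality.** The Introduction also cites 17% to 24% from the international cohort. At those rates 1,000 infants give 170 to 240 deaths. With 10 candidates in the 70% set that is 119 / 10 = 11.9 to 168 / 10 = 16.8, so the rule is met. With 20 in the full cohort it is 170 / 20 = 8.5 to 240 / 20 = 12.0. With 30 it is 5.7 to 8.0. The shortfall in Step 3 thus depends on the plan's own 12.6%, and it disappears once mortality reaches 100 / 700 = 14.3%.

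**Step 6: do these figures carry over to the tasks in 6.2?** No event rate is stated for severe NARDS. Assuming 10%, 30% or 50%, 30 clinical candidates would have 100 / 30 = 3.3, 300 / 30 = 10 or 500 / 30 = 16.7 events each in the full cohort, and 2.3, 7 or 11.7 in the 70% set. The result ranges from well short to comfortably met, so the mortality figures say nothing firm about that task.

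**The case against.** The strongest reply is that the one model that was sized meets its rule. Section 3.6.2 limits itself to in-hospital mortality, logistic regression and up to 10 potential predictors, and 126 expected deaths give 12.6 each. Nowhere does the article say that this model selects from a larger pool. That stands, and the arithmetic in 3.6.2 is not in question.

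A reader might go further and infer that the criterion is missed about threefold for the models actually fitted, because Table 1 lists dozens of variables. The documents do not support that, for four reasons:

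- Table 1 lists what a registry collects. It is not a statement of model inputs, and some entries, such as sepsis, severe sepsis and septic shock, are grades of one condition.
- Section 6.2 narrows candidates by clinical relevance and timing before Elastic Net is applied. The resulting number is not given.
- The 126 deaths belong to the in-hospital mortality model. The tasks in 6.2 have other endpoints without stated event rates.
- The rule is stated for logistic regression. It is not a direct test of penalised regression, latent-factor inputs or tree-based learners, and a low ratio of events to raw omics features is not in itself a failed criterion for them.

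Two further replies have some force. Section 6.1 does not state that univariate results decide entry to the multivariable model; that is one reading of its sequence. Section 6.3 also plans validation, calibration and TRIPOD reporting. These measures help to show overfitting, but they do not make the sample size calculation cover models that it was not built for.

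A full candidate list may reasonably be left to a statistical analysis plan. What remains is a limit on which the stated sample size depends, given in one section of the article and absent from the sections that describe the modelling.

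**Conclusion.** The point holds in a limited form. The calculation supports an in-hospital mortality logistic model with at most 10 candidate parameters fitted on the full cohort, and nothing else in the modelling plan. That model is not itself one of the two primary prediction tasks in 6.2.

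The size of any shortfall is conditional. At 12.6% mortality and 1,000 infants with complete data, developing the model on the 70% set gives 8.8 deaths per parameter instead of 10, even with exactly 10 candidates. With a larger pool in the full cohort the ratio falls to 6.3 at 20 candidates, 4.2 at 30 and about 3.4 if all 37 Table 1 items entered. No particular shortfall is established, because the candidate count is not stated. None of these figures applies to the severe-NARDS, long-term or omics models.

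For those models the gap is of another kind: the statement that 1,000 also provides power for further secondary analyses has no calculation shown behind it.

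**What to change.** - **3.6.2 and 6.1:** state that the 10 counts candidate parameters, including each extra category of a multi-level variable. Restrict the unpenalised mortality model to at most 10 parameters chosen on clinical grounds before the data are examined, and do not use univariate results to choose them. Section 6.5 already names gestational age, birth weight z-score, sex and major comorbidities as adjustment covariates. If the four comorbidities named in 3.8.4 (hsPDA, IVH, sepsis, NEC) are meant, 3 + 4 = 7 of the 10 places are taken.
- **6.3:** state that this model is fitted on the full cohort and validated by bootstrap, which 6.3 already plans. This keeps the expected 126 deaths in place of 88.
- **3.6.2, 6.2 and 6.4:** state that the machine-learning and omics models are not covered by the calculation. Remove or qualify the claim of sufficient power for the remaining secondary analyses.

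These are wording changes and need no extra enrolment. The cost is a shorter predictor list in the main regression model. The wider searches can go ahead, described as outside the sample size justification.

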### Model evaluation and validation

6.3

Model performance will be evaluated using the area under the receiver operating characteristic curve (AUROC), sensitivity, specificity, calibration plots, Brier score, and, where applicable, precision–recall curves for imbalanced outcomes. Internal validation will be performed using a robust strategy: randomly partitioning the cohort into a 70% Discovery Set and a 30% Internal Validation Set at baseline. The validation set will serve as an independent internal check for model generalizability. We will also perform internal validation using cross-validation and bootstrap resampling, strictly adhering to the TRIPOD reporting guidelines for predictive models (38). Where feasible, temporal or center-level external validation (or internal holdout by center) will be undertaken to assess generalizability.

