While innovative, our study has limitations. A primary limitation is the potential for significant selection bias, as the study is confined to Shenzhen, a single, economically developed “special economic zone” in China. The healthcare resources, patient demographics, and socioeconomic status in this region are not representative of the broader diversity across China, including rural or less developed areas. This may result in a study cohort with better outcomes than the national average, and therefore, our findings must be interpreted with caution and require validation in more geographically and socioeconomically diverse populations before they can be generalized. Loss to follow-up is another concern in longitudinal work. We have instituted multiple strategies to minimize dropout and will address any residual missing data with modern statistical methods like multiple imputation and inverse probability weighting, accompanied by sensitivity analyses. While the multicenter nature of the study introduces heterogeneity in clinical management, this is also a methodological opportunity. By meticulously documenting variations in interventions (e.g., ventilation strategies, surfactant use), we can leverage advanced statistical methods, such as propensity score matching or inverse probability weighting, to conduct comparative effectiveness analyses in a real-world setting. This can generate valuable hypotheses for future randomized controlled trials.

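### The 100 deaths required for the in-hospital mortality model are counted over the whole cohort, but section 6.3 as worded leaves only 70% of the cohort for fitting: about 88 deaths at 1,000 infants, or 8.8 per predictor against the plan's own 10

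*Protocol article*

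**What the plan says.** Section 3.6.2 of the protocol article gives one formal calculation, for "the development of a multivariable prediction model for in-hospital mortality". The criterion is "a minimum of 10 events per predictor variable for logistic regression", and from it follows "anticipating up to 10 potential predictors, a minimum of 100 mortality events is required". The planning rate is introduced with "Utilizing a conservative estimated mortality rate of 12.6% as derived from previous studies", and the result is that "a total cohort of at least 794 patients would be required to achieve the desired statistical power". The target is then raised to 1,000. Two reasons are given for the increase: incomplete data and the needs of other secondary analyses. A hold-out sample is not among them.

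Section 6.3 describes internal validation as "randomly partitioning the cohort into a 70% Discovery Set and a 30% Internal Validation Set at baseline". The 30% is meant as an independent check. Cross-validation and bootstrap are to be done as well, and validation over time or by centre where feasible. Section 6.4 repeats a 70/30 split for the biomarker models.

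Section 6.2 says "Two primary prediction tasks will be addressed". These are severe NARDS within 72 hours, and long-term prognosis at 24 and 36 months. In-hospital mortality is not one of them.

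**The concern.** An events-per-predictor rule concerns the data on which a model is fitted. Section 3.6.2 applies it to all infants, whereas 6.3 as worded fits on 70% of them. The two sections therefore do not describe the same development sample, and the minimum that 3.6.2 sets is not delivered at the planning rate it uses. What is at stake is the only formal justification of the sample size, and a model that would be somewhat more prone to overfitting than the plan claims.

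Two smaller faults lie in the same text. The calculation is described as achieving statistical power, but it uses no significance level, effect size or power; it is a count of events. And the model that drives the sample size does not appear among the prediction tasks of 6.2, so a reader cannot tell which development and validation scheme it falls under.

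**Working it through.** **Inputs.** From 3.6.2: 10 events per predictor, up to 10 predictors, mortality 12.6%, minimum 794, target 1,000. From 6.3: 70% for development, 30% for validation. From the Introduction, as a range check: mortality of 17%–24% in the international cohort.

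**1. The plan's own figure.** Events required: 10 × 10 = 100. Cohort: 100/0.126 = 793.7, rounded up to 794. The plan's figure reproduces exactly, so there is no arithmetic slip in 3.6.2.

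**2. Deaths in each part after a 70/30 split** (infants × share × mortality, all records usable):

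| Infants | Mortality | All deaths | Development (70%) | Per predictor (10) | Validation (30%) |
|---|---|---|---|---|---|
| 794 | 12.6% | 100.0 | 70.0 | 7.0 | 30.0 |
| 1,000 | 12.6% | 126.0 | 88.2 | 8.8 | 37.8 |
| 1,000 | 17% | 170.0 | 119.0 | 11.9 | 51.0 |
| 1,000 | 24% | 240.0 | 168.0 | 16.8 | 72.0 |

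**3. What would satisfy the rule inside the 70%.**
- Larger cohort at 12.6%: 100/(0.70 × 0.126) = 1,133.8, so 1,134 infants with complete data.
- Higher mortality at 1,000 infants: 100/700 = 14.3%.
- Fewer predictors at 1,000 infants and 12.6%: 88.2/10 = 8.8, so at most 8 candidate parameters.

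**4. Chance of reaching 100 deaths.** If each infant's risk is 12.6% (binomial), the probability of at least 100 deaths is about 0.10 among 700 infants and about 0.995 among 1,000. Whether the split applies therefore largely decides whether the requirement is met.

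**5. The margin.** The step from 794 to 1,000 covers a loss of 1 − 794/1,000 = 20.6% of records. Section 3.6.2 already assigns that step to incomplete data and other analyses. The 88 deaths assume that none of it is used up, so 88 is a best case at 12.6%.

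**The case against.** The strongest reply is that the split was never meant for this model. Section 3.6.2 speaks of logistic regression, which sits in 6.1, where no split is stated. Section 6.2 begins by going beyond conventional regression, and 6.3 follows from there. On that reading the mortality model uses all 126 expected deaths and meets the rule at 12.6 per predictor. The reading is possible, but the text does not state it: 6.3 partitions the cohort as a whole and exempts no model. The conclusion is therefore conditional on the split applying.

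Other parts of the reply also stand. The 12.6% is the lowest mortality the article cites, and at the international 17% the shortfall is gone. Ten predictors is a ceiling, and eight would comply. Bootstrap and cross-validation are already listed, although 6.3 adds them to the split and does not put them in its place. The sized model is a secondary objective, and the descriptive primary objective is untouched.

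Three stronger readings are tempting, and the document does not support them.
- A reader might infer that about 38 validation deaths are too few to judge the AUROC > 0.85 target. That target is set for severe NARDS (section 4.3) and, in the abstract, for severe NARDS and long-term adverse outcomes. It is not set for in-hospital mortality. The article gives no expected rate of severe NARDS, so the precision for that target cannot be worked out from a count of deaths.
- A reader might infer that mortality will fall below 12.6%, because the Discussion says of the single-city setting: "This may result in a study cohort with better outcomes than the national average". That is a possibility, not a forecast. Nor can the exclusion of deaths in the first 24 hours be used to lower the rate, since the exclusions of the cohort behind the 12.6% are not shown.
- A reader might infer that the study as a whole is undersized. The calculation concerns one secondary model and misses a rule of thumb by about one event per predictor.

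**Conclusion.** The point holds in conditional form. If the 70/30 split applies to the mortality model, as 6.3 is worded, the plan does not deliver its own minimum of 100 development deaths: it expects about 88 at the target and 70 at the stated minimum cohort. This rests on three assumptions: the plan's 12.6% mortality, complete records on all 1,000 infants, and the full ten candidate predictors. The gap closes at mortality of about 14.3% or more, with eight or fewer candidate parameters, or if the model is fitted on everyone.

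The fault is an inconsistency between two sections, not an error in the 794. The unsupported reference to power and the mismatch with 6.2 are real but are matters of wording. Severity: should be fixed, because the remedy is cheap and the objective concerned is secondary.

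**What to change.** 1. State in 3.6.2 and 6.3 that the in-hospital mortality model is developed on all enrolled infants, with 126 expected deaths at 12.6%, or 12.6 per predictor.
2. For this model, make optimism correction by bootstrap or cross-validation the primary internal validation in place of the single random split, and repeat every selection step within each resample.
3. Supplement this with internal–external validation by centre, leaving out each of the nine units in turn and pooling the results. Pooling is needed because a held-out centre would have on average only 126/9 = 14 deaths.
4. If the split is kept, restate 3.6.2 as about 88 development deaths at 1,000 complete records, and limit the model to at most 8 candidate parameters.
5. In 3.6.2, replace the reference to statistical power with the events-per-predictor criterion that was actually used.
6. Either add in-hospital mortality to the prediction tasks in 6.2, or base the calculation on the tasks listed there.

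The cost is wording and some computing time, with no extra infants. The small downside of items 1 and 2 is that there will be no single held-out AUROC to quote for this model. The choice should be settled before any partition is drawn.

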#### Biomarker discovery and validation

2.2.3

To discover and validate novel biomarkers for NARDS by linking our longitudinal biobank to clinical outcomes. This includes:
Identifying predictive proteomic and metabolomic signatures for severe NARDS (sNARDS) using longitudinally collected plasma/serum samples.Characterizing the local inflammatory milieu through transcriptomic analysis of tracheal aspirates.Performing a genome-wide association study (GWAS) using genomic DNA from blood to identify genetic variants associated with NARDS susceptibility and severity.

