#### Biospecimens collection and management

3.8.2

The collection of biospecimens is a key voluntary sub-study of the SZ-NARDS cohort. Participation requires a separate, specific written informed consent from the infant's legal guardians, ensuring they are fully aware of the distinct nature of the biobanking component.

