### Biomarker and predictive modeling outcomes

4.3

The primary outcomes related to the multi-omics biomarker analysis are:
The identification and validation of a proteomic and/or metabolomic signature, derived from baseline (within 24 h of diagnosis) plasma/serum samples, that demonstrates high accuracy [defined as an Area Under the Receiver Operating Characteristic Curve (AUROC) > 0.85] for predicting the development of severe NARDS (OI ≥ 16) within 72 h of diagnosisThe discovery of novel genetic variants *via* a Genome-Wide Association Study (GWAS) that are significantly associated with susceptibility to NARDS and/or in-hospital mortality.

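### The 1,000-patient target is said to give adequate power for the other secondary analyses, but this does not hold for the in-hospital mortality GWAS

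*Protocol article*

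**What the plan says.** Section 3.6.2 sizes the cohort for a model of in-hospital mortality, using "a minimum of 10 events per predictor variable for logistic regression, and anticipating up to 10 potential predictors", so that "a minimum of 100 mortality events is required". It continues: "Utilizing a conservative estimated mortality rate of 12.6% as derived from previous studies", and concludes that "a total cohort of at least 794 patients would be required to achieve the desired statistical power". The target is then raised to 1,000 for two reasons. One is incomplete data. The other is "to ensure adequate power for other secondary analyses, the target sample size is set at 1,000 patients". The analyses covered by that second reason are not named, and no calculation is given for any of them.

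The GWAS is one of the secondary objectives. Section 2.2.3 lists it among the biomarker aims: "Performing a genome-wide association study (GWAS) using genomic DNA from blood". Section 4.3 then makes it one of the primary outcomes of the multi-omics work, namely variants "that are significantly associated with susceptibility to NARDS and/or in-hospital mortality". DNA is available only from families who give a separate consent: "The collection of biospecimens is a key voluntary sub-study of the SZ-NARDS cohort" (Section 3.8.2). Expected uptake is not stated. The only significance level in the article is a two-sided 0.05 (Section 6.1).

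**The concern.** The article asserts a property of the design (1,000 is enough for the other secondary analyses). It is therefore not a detail deferred to a later document, and it can be tested against the plan's own mortality rate. A ten-events-per-variable rule fixes neither a significance level nor an effect size, so it carries no information about power for a scan of the whole genome.

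Interpretation is what is at stake. When a primary biomarker outcome rests on a sample size declared adequate, a null scan can easily be taken as evidence against a genetic contribution to death. If the study could not have detected effects of moderate size, that reading is unsafe. Conversely, a variant that does reach significance in such a study will carry an inflated odds ratio.

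**Working it through.** **The plan's own figure.** 10 events x 10 predictors = 100 deaths; 100 / 0.126 = 793.65, rounded up to 794. This reproduces exactly. At the target, 1,000 x 0.126 = 126 deaths and 874 survivors.

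**Inputs from the article.** Target 1,000 and mortality 12.6% (3.6.2); alternative mortality 17% to 24% from the international cohort (Introduction), which gives 170 to 240 deaths; voluntary biobank consent (3.8.2).

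**Inputs assumed here.** A two-sided threshold of 5e-8 (the conventional genome-wide level), an odds ratio (OR) of 1.5 per allele, minor allele frequency (MAF) 0.05 to 0.50, and 60% consent in one scenario.

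**Formula.** Allelic comparison of two proportions with pooled variance under the null. With MAF m in survivors:
- case allele frequency p1 = OR x m/(1 - m) / [1 + OR x m/(1 - m)]
- n1 = 2 x deaths alleles, n2 = 2 x survivors alleles, pbar = (n1 p1 + n2 m)/(n1 + n2)
- SE0 = sqrt[pbar(1 - pbar)(1/n1 + 1/n2)], SE1 = sqrt[p1(1 - p1)/n1 + m(1 - m)/n2]
- power = Phi[(p1 - m - z x SE0)/SE1], with z = 5.451 for 5e-8

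**Worked case, m = 0.3, OR 1.5.** p1 = 0.6429/1.6429 = 0.3913. The difference is 0.0913, and pbar = 0.126 x 0.3913 + 0.874 x 0.3 = 0.3115. With n1 = 252 and n2 = 1,748, SE0 = 0.0312 and SE1 = 0.0326. Then (0.0913 - 5.451 x 0.0312)/0.0326 is about -2.41, and Phi gives 0.79%.

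**Power (%) for OR 1.5 at 5e-8:**

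| Deaths v survivors | MAF 0.05 | 0.10 | 0.20 | 0.30 | 0.40 | 0.50 |
|---|---|---|---|---|---|---|
| 126 v 874 (12.6%, all genotyped) | 0.03 | 0.13 | 0.49 | 0.79 | 0.81 | 0.58 |
| 170 v 830 (17%) | 0.05 | 0.23 | 1.1 | 1.9 | 2.2 | 1.7 |
| 240 v 760 (24%) | 0.07 | 0.43 | 2.4 | 4.8 | 5.8 | 4.9 |
| 76 v 524 (12.6%, 60% consent) | 0.01 | 0.03 | 0.09 | 0.12 | 0.11 | 0.07 |

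**Check by simulation.** An additive logistic model with a score test (N = 1,000, 12.6% mortality, 20,000 replicates) gives 0.76%, 0.82% and 0.51% at MAF 0.30, 0.40 and 0.50.

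**Smallest OR with 80% power, 126 deaths.** The formula gives 2.87 at MAF 0.1, 2.45 at 0.2, 2.33 at 0.3 and 2.34 at 0.4. The simulated score test is slightly less favourable: about 2.4 at MAF 0.3-0.4 and about 3.1 at 0.1. At 60% consent the formula gives about 3.0 (MAF 0.3-0.4) to 3.6 (MAF 0.1). Simulation there gives 75% power at OR 3.0 and MAF 0.3, and 61% at OR 3.6 and MAF 0.1, so that range is if anything optimistic.

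**Sensitivity to the assumptions.** At OR 2.0 with 126 deaths, power is 2% to 38% over the same MAF range. At a relaxed threshold of 1e-5, power for OR 1.5 is 0.6% to 8.3%. For 80% power at OR 1.5 and 5e-8, about 551 deaths are needed at MAF 0.4 and 1,201 at MAF 0.1. At 12.6% mortality that is about 4,400 to 9,500 infants.

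**Inflation of a hit.** At MAF 0.3 with 126 deaths, significance needs an observed difference of about 5.451 x 0.0315 = 0.172 (SE0 re-evaluated at that difference). That is a case frequency of 0.472 and an observed OR of (0.472/0.528)/(0.3/0.7), about 2.1, even if the true OR is 1.5.

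**The case against.** The article gives no genome-wide threshold, effect size or allele frequency, and a power specification for genetics is often left to a sub-protocol. Both 5e-8 and OR 1.5 are therefore outside inputs. That is correct, and the result must be labelled conditional on them. It does not rescue the clause, because adequacy is asserted in the article itself. The only stated alternative, 0.05, would give 36% to 85% power for one pre-chosen variant but cannot serve a genome-wide scan.

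A reader might infer that 126 deaths is a ceiling. It is so only at the planning rate. The article calls 12.6% conservative, cites 17% to 24% elsewhere, and its abstract speaks of more than 1,000 infants. With more deaths, power can exceed 1%, though it stays below 6% for 1,000 infants.

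A reader might also infer that the whole GWAS is underpowered. The document does not support that. Susceptibility power depends on a control group that is not described. With an assumed 1,000 controls, the same formula would give 10%, 73% and 82% for OR 1.5 at MAF 0.1, 0.3 and 0.5, so the mortality result cannot be carried over. Severity could be analysed on the continuous oxygenation index, and the share of severe cases is not given.

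Finally, the arithmetic behind 794 is right, and no passage says that a null scan will be read as absence of association. That consequence is a risk of the wording, not a stated intention.

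**Conclusion.** The power clause in Section 3.6.2 is unsupported by the calculation shown, and it is wrong for the in-hospital mortality GWAS. With full genotyping, power for an assumed OR of 1.5 at an assumed 5e-8 is under 1% at the planned 12.6% mortality and under 6% at 17% to 24%. Incomplete biobank consent reduces it further. The sample suits only large effects. The conclusion rests on the two assumed inputs, but it is not delicate: neither OR 2.0 nor a threshold of 1e-5 brings power anywhere near 80%. It covers the mortality phenotype only. Nothing is concluded about susceptibility, and the target of 1,000 remains sound for the events-per-variable purpose for which it was derived.

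**What to change.** - In Section 3.6.2, delete the clause about power for other secondary analyses, or limit it to analyses for which power is shown. The allowance for incomplete data can stay as the reason for going from 794 to 1,000.
- State the GWAS significance threshold and the smallest detectable OR at the expected number of genotyped deaths. With full consent and 126 deaths at 5e-8, this is about 2.3-2.4 at MAF 0.3-0.4 and about 2.9-3.1 at MAF 0.1. Give the assumed consent rate and recalculate for it.
- In Section 4.3, label the within-cohort mortality GWAS exploratory, and say that a null result will not be read as absence of association.

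The cost is a less favourable stated figure. No patients, samples or assays are added.
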